#### Feasibility and Pilot Study (Phase 3)

In phase 3, the co-designed self-help app will be delivered to all recruited midadolescents, who will be free to download the app on their personal iOS or Android device. For 1 month, participants will be invited to use the self-help app exploring the different contents and functionalities weekly, and to adopt these newly learned competencies in their daily life.

At the end of the self-help app use (T3; postintervention), feasibility will be investigated: (1) administering an adolescent-adapted version of the “Mobile App Rating Scale user version” (uMARS) [54], together with open-ended questions exploring the adolescents’ opinion about the app (eg, “Can you tell me about your experiences using the App?”; “What did you like most/least?”). The uMARS is a 20-item self-report measure of the perceived quality of apps, which includes 4 objective quality subscales (ie, engagement, functionality, aesthetics, and information quality) and 1 subjective quality subscale.

At this last time point (T3; around months 18-20), we will gather preliminary data on the effectiveness of the app intervention, administering the self-report questionnaires measuring the primary and secondary outcomes mentioned in phase 1. Given that the latter time point for the longitudinal study (ie, T2) falls a little before the start of phase 3, data on outcomes collected at that time point will be used as preintervention scores.

As a last step of this project, the app (eg, contents, features, and design) will be adapted on the basis of the emerging results.

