### Sample Size Estimation

For the longitudinal study (phase 1) a convenient sample of 1216 adolescents will allow detection of a small effect size for regression-based models according to potential predictors (α=.05; power=0.80). After a 25% increase to account for potential dropouts, the estimated final number of participants will be 1520 adolescents.

For the HRV measure, to detect a medium effect size with 80% of power [55], at least 61 healthy adolescents need to be recruited. For the analysis of the genotyping serotonin transporter polymorphisms 5-HT1AR and 5-HT2AR, based on the effect sizes reported in Matsunaga et al [47], an a priori power analysis estimated that 191 participants would be necessary to detect a small-to-medium effect size (α=.05; power=0.80).

For phase 2, applying the criteria of data saturation, around 12 FGs distributed across schools in Italy are expected to be sufficient to explore all the relevant topics. The final number will be adjusted according to the data saturation criteria. As for the co-design workshops, a purposive sample of around 20 midadolescents is evaluated sufficient.

For phase 3, all the adolescents who took part in phase 1 of the project will be invited to participate in this phase. Considering that longitudinal studies on unguided self-help interventions report up to 63% of drop-out rates [56] and that this phase will start after several months from the first recruitment, we expect a final sample of around 400 adolescents participating in this phase, which is considered sufficient for feasibility and pilot aims.

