In line with a mixed methods approach [71], quantitative and qualitative results will be synthesized and merged in order to achieve a better understating of the PSMU. Indeed, qualitative results will be used to deepen our understanding of the PSMU phenomenon, corroborating the findings from the quantitative design and/or adding potential different topics.

As for phase 3, feasibility (ie, uMARS mean scores and app usage) will be investigated through simple descriptives, examining whether participants met the thresholds for good feasibility: (1) mean uMARS subscale scores≥70% of the total will be considered indicative of good feasibility [72]; examining the app use (with ≥75% of participants with ≥10 app sessions considered indicative of a good feasibility) [72]. We will have a deeper understanding of the app feasibility by synthesizing the qualitative results. We will further examine whether the self-help app led to an actual change in primary and secondary outcomes through 3-level piecewise regression models, using the 4-time points from baseline (as defined in phase 1; T0) up to posttreatment (T3; M18-M20). To further strengthen these analyses, we will compute both a Reliable Change Index and a Clinically Significant Change for each participant [73,74]. These methods are used to test whether a change over time (in our case, from pre- to posttreatment) may be considered reliable (ie, taking into account the measure’s internal reliability) and clinically significant (eg, the posttreatment scores are within the boundaries of nonpathological scores).

Quantitative analyses will be performed using SPSS (version 29; IBM Corp), Hierarchical Linear Models (version 8.2; Scientific Software International, Inc), and MPLUS (version 8.4; Muthén & Muthén).

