This study has some limitations. First, data will only be collected among Italian participants, thus our results may not be generalizable to other populations and cultures. Second, most of the measures used in this protocol are self-report, thus subjected, among the others, to response and social desirability biases [81]. The effectiveness of the SMART app will be tested through a nonrandomized design, thus limiting our possibility to make causal inferences. Finally, we have chosen to investigate only a fraction of the potential biopsychosocial predictors of PSMU among adolescents, thus we may have missed other important determinants of this problematic behavior.

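### The phase 3 piecewise model has one post-app point, no concurrent comparison and no app-use term, so it can show change associated with the app but not that the app caused it

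*Protocol article*

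**What the plan says.** Table 1 describes phase 3 as a single-arm feasibility pilot with a pre-post evaluation. Under Feasibility and Pilot Study (Phase 3), the app "will be delivered to all recruited midadolescents, who will be free to download the app", and participants are invited to use it for one month. T3 comes when app use ends (months 18-20), and T2 (months 13-15) supplies the pre-intervention scores. Under Sample Size Estimation all phase 1 adolescents are invited, and "we expect a final sample of around 400 adolescents participating in this phase".

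The Statistical Analyses section then states: "We will further examine whether the self-help app led to an actual change in primary and secondary outcomes". The tool is a 3-level piecewise regression on T0 to T3, supplemented by a Reliable Change Index and a Clinically Significant Change for each participant. App usage appears in that section as a feasibility measure and is not named as a term in the outcome model.

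Two other places bear on this. The Objectives section words the phase 3 hypothesis as an association between greater app use and more functional social media use. The limitations paragraph of the Discussion concedes a "nonrandomized design, thus limiting our possibility to make causal inferences".

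**The concern.** The question in the analysis section is causal, but the design cannot answer it. Nobody is described as an unexposed comparison over the T2-T3 interval, and that interval ends in a single measurement. Anything that moves the whole cohort off its T0-T2 line between T2 and T3 appears in the same coefficient as the app. Adolescents who take up the app because their T2 score was unusual would also drift back without it.

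The Reliable Change Index and Clinically Significant Change do not separate these sources. They deal with measurement error and cut-offs in individual scores, not with time effects that everyone shares.

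The analysis as described also does not test the hypothesis as stated: the hypothesis is about amount of app use, and the model names no such term. At stake is the effectiveness signal, which the Discussion says may guide later randomised trials.

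**Working it through.** **The plan's own figures.** Phase 1 needs 1216 ("a convenient sample of 1216 adolescents will allow detection of a small effect size for regression-based models"). "After a 25% increase to account for potential dropouts", 1216 × 1.25 = 1520, which reproduces "the estimated final number of participants will be 1520 adolescents". This allows for a loss of 1 − 1216/1520 = 20%. If 25% of 1520 were lost, 1520 × 0.75 = 1140 would remain.

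No formula is given for the 400. The article notes that "longitudinal studies on unguided self-help interventions report up to 63% of drop-out rates". Retention of 37% gives 1520 × 0.37 = 562, or 1140 × 0.37 = 422, so 400 is a rounded judgement.

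**Share taking part.** 400/1520 = 26.3% of the recruitment target; 400/1216 = 32.9%; 400/1140 = 35.1%.

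**Length of the second segment.** Shortest gap 18 − 15 = 3 months, longest 20 − 13 = 7 months, against one month of app use. Most of the segment can be time without the app.

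**What the piecewise model removes.** With waves T0, T1 and T2 before the app and only T3 after it, the mean structure is a line through T0-T2 plus one free parameter that T3 alone determines. Drift that continues the T0-T2 line is absorbed. A departure of size s from that line at T3, shared by all, enters the second-segment estimate one for one.

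**Is nonlinear drift plausible?** Enrolment began in December 2023 and follow-up ends within May 2025. Assume December 2023 is month 3. Then T0 is December-February, T1 May-July, T2 October-December and T3 March-May; month 20 is May 2025, which agrees with the stated end. The waves fall at different points of the season and school year, and such effects need not lie on a line.

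**Size of the risk.** Assumptions: 400 users, no true app effect, T2-T3 correlation ρ = 0.6, outcome in SD units, simple paired comparison.
- SE of mean change = √(2(1 − ρ)/400) = √(0.8/400) = 0.0447.
- P(significant in the direction of the shift) = Φ(s/SE − 1.96).
- s = 0.05, 0.10, 0.15 gives 20%, 61%, 92%.

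For regression to the mean, if users start c SD from the cohort mean because of a chance element in the T2 score, the expected change is c(1 − ρ).
- c = 0.2: 0.2 × 0.4 = 0.08 SD, significant in 43% (34% to 52% for ρ from 0.7 to 0.5).
- c = 0.3: 0.12 SD, significant in 77% (64% to 85%).

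These figures show the order of magnitude for a simple T2-T3 comparison. They are not the error rate of the piecewise model.

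**What non-users at T3 could add.** If 1140 remain, non-users number 1140 − 400 = 740. Minimum detectable d = (1.960 + 0.842) × √(1/400 + 1/n). Assumed design effect for classes: 1 + (20 − 1) × 0.05 = 1.95, which multiplies d by √1.95.

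| Non-users responding | Detectable d | Power for d = 0.20 | Detectable d with design effect |
|---|---|---|---|
| 740 (all) | 0.17 | 90% | 0.24 |
| 370 (half) | 0.20 | 79% | 0.28 |
| 200 | 0.24 | 64% | 0.34 |

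If 1216 reached T2 there would be 816 non-users; 740 is the safer figure.

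**Items to be answered.** Table 2: 6 + 10 + 5 = 21 for the primary and two secondary outcomes.

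**The case against.** The design is declared openly. The article calls phase 3 a single-arm pilot, calls its effectiveness findings preliminary, admits that the lack of randomisation limits causal inference, and leaves effectiveness to future trials. Not having a concurrent control is a legitimate choice for a pilot. Three pre-intervention waves are more than most pilots have and deal with steady ageing. Analysis sets and model terms may be set out in a fuller plan that is not shown. All of this stands, and it limits the point to the wording of the conclusion and a low-burden strengthening of the analysis.

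Some stronger readings are tempting but go beyond the text:
- **Only app users answer at T3.** The timing of T3 and the expected 400 imply this. No sentence says it, and Table 2 lists T3 for the three outcomes without a subsample note.
- **The T0-T2 trend comes from the whole cohort and the T2-T3 segment from joiners.** The analysis set is not given. It may be phase 3 participants throughout.
- **Every shared change would be reported as app effect.** Linear drift is removed; only departures from the line remain.
- **A comparison group is nearly free.** The article gives no cost. It describes the school-hours survey for the phase 1 waves only, and access to non-participants at months 18-20 is unknown.
- **Non-users would cure the selection problem.** They are adolescents who were offered the app and declined, so they are self-selected too.

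The general caveat in the Discussion does not settle the matter, because the analysis section still poses the causal question and names no term that tests the associational hypothesis.

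**Conclusion.** The point holds in limited form. The design supports a statement that outcomes changed in association with app use. It does not support the causal statement in the analysis section, which is at odds with both the associational hypothesis and the stated limitation.

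About 26% of the recruitment target is expected to take part, by choice, and one post-app measurement 3 to 7 months after T2 carries the whole effect estimate. Under the assumptions above, a nonlinear shared shift of only 0.10 SD would give a significant change in about six of ten simple pre-post comparisons with no app effect. The correlation, the size of the shift and the calendar are assumptions, so this is an illustration and not an estimate of bias. The mismatches in wording and model terms need no assumption.

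This is an improvement worth making before T3, which still lies ahead in the article (T0 and T1 were complete as of July 2024). It is not a fatal flaw in a feasibility pilot.

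**What to change.** 1. **Wording.** In the phase 3 analysis, replace the causal phrasing with *was associated with change*. No cost.
2. **Model.** Add an interaction between app use and the second segment (T2-T3) to the piecewise model, adjusted for T0-T2 outcome level and T0 covariates. Usage is already recorded for the feasibility criterion, so the cost is one model term and its adjustment. This aligns the analysis with the stated hypothesis.
3. **T3 assessment.** State who is assessed at T3. Where schools allow, offer the 21 existing items to every T2 respondent, whether or not the app was downloaded. Report the adjusted user versus non-user contrast as exploratory, with the non-user response rate.

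The price of the third step is extra survey burden and an unknown response among non-users: 740 if 1140 remain and all respond, fewer in practice. The contrast would address time trends shared by both groups. It would not remove self-selection, and the report should say so.

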## Introduction

### Background

According to the World Health Organization, one-sixth of the global population is composed of adolescents, and this number is expected to rise through 2050 [1]. Unfortunately, 1 in 7 adolescents experience mental health conditions, which remain largely unrecognized and untreated. Also, given the widespread use and pervasiveness of new technologies among adolescents, it is not surprising that 60.43% of Italian adolescents report an intense or a problematic social media (SM) use (PSMU) [2] and, although to our knowledge, no estimations regarding the direct or indirect financial cost or societal burden of PSMU are currently available, it has been hypothesized that PSMU may have relevant costs both for individuals (eg, mental and physical health, social functioning) and societies (eg, direct health care costs and indirect costs following productivity losses).

SM is made up of various digital user-driven platforms (eg, Facebook, TikTok, Instagram) that facilitate connectivity and engagement between individuals as well as allow to create and share user-generated content [3]. PSMU is considered an etiologically complex behavior associated with psychological distress, although this relation is far from being completely understood [4] and the conceptualization of PSMU is still debated. To date, the absence of a commonly accepted definition could be linked to the rapidly changing nature of SM as well as to the inconsistent results obtained by prior research on PSMU among adolescents [5]. Technology and SM are an integral part of the daily life of today’s teenagers, who use them to create a virtual space to satisfy their needs for communication, social contact, belonging, comparison, and self-realization. However, some scholars defined PSMU as an “addictive-like” behavior (eg, associated with salience, tolerance, withdrawal, and relapse) [6], hierarchically arranged (ie, with different levels of excessive or disordered use) and whose main characteristic is a lack of self-regulation in one’s own SM use [4].

Nonetheless, the adoption of an addiction paradigm to describe PSMU has been criticized [7].

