### Participant Recruitment and Setting

The target group (adolescents aged 14-18 years) will be actively involved in the various actions of each phase. Participants will be recruited from schools (ie, secondary school), in the north, central, and south Italy. Each research team will select schools (on a voluntary basis or following previous collaborations) and interact with stakeholders (regional and local school offices, school communities) to obtain their availability for participation. Attention will be given to contacting schools located in particularly disadvantaged areas and to include students with different sociodemographic and cultural backgrounds and levels of vulnerability. At each participating school, adolescents may participate in the different phases of the study.

The following inclusion criteria will be followed for participation in each included school: (1) having an age between 14 and 18 years, (2) having signed the consent form for the study participation (ie, consent to participate for adolescents less than 18 years signed by both parents—or legal representatives—or by the adolescent when 18 years); having sufficient knowledge of the Italian language.

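### The individual reliable-change and clinical-change counts cover only the app interval and have no app-free reference, so ordinary fluctuation over about five months can pass for app benefit

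*Protocol article*

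**What the plan says.** All references are to the protocol article.

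- **Indices and interval.** The Statistical Analyses section states that "we will compute both a Reliable Change Index and a Clinically Significant Change for each participant". They are used to "test whether a change over time (in our case, from pre- to posttreatment"), and are introduced as a way to reinforce the phase 3 regression models of change in the outcomes.
- **Reliable change.** The change "may be considered reliable (ie, taking into account the measure’s internal reliability"). No reliability value or cutoff is given.
- **Clinical significance.** The only criterion shown is an example: "clinically significant (eg, the posttreatment scores are within the boundaries of nonpathological scores"). No condition on the starting score is stated.
- **Timing.** Under Feasibility and Pilot Study (Phase 3), the T2 "data on outcomes collected at that time point will be used as preintervention scores". The post score is taken at T3: "At this last time point (T3; around months 18-20"). The notes to Table 2 put T2 at months 13-15. App use lasts one month.
- **Population.** Participant Recruitment and Setting requires "having an age between 14 and 18 years", signed consent and sufficient Italian. There is no entry threshold on problematic use, and the app goes to all recruited adolescents. Table 1 describes phase 3 as single-arm, and the Sample Size Estimation section expects around 400 participants.
- **Earlier waves.** T0 and T1 enter phase 3 only through the piecewise regression models.

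**The concern.** An index built on internal reliability asks whether a difference is larger than measurement error would produce. It does not ask whether the difference is larger than adolescents' scores normally move over five months. In a single-arm study nothing else in the individual counts separates natural movement from an app effect. An inert app would therefore still yield a list of adolescents labelled reliably improved, and possibly a rate above what readers expect by chance.

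Clinical significance has a related weakness. These indices presuppose a person who starts in the pathological range and leaves it, but this sample includes adolescents who never were in that range. How they are classified, and whether they sit in the denominator, changes the reported rate without any change in what the app does.

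At stake is how the pilot's signal is read. The Discussion says that the results may guide later randomized trials.

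**Working it through.** **Plan's own figure.** The plan states no expected rate of reliable or clinically significant change, so there is none to reproduce. The expected 400 participants are taken as given.

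**Length of the interval.** T0 is months 3-5, T1 months 8-10, T2 months 13-15 and T3 months 18-20. The midpoints are 4, 9, 14 and 19, so each interval is about 5 months. T0-T1 and T1-T2 are free of the app.

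**Share reliably improved if the app does nothing.** Assumptions, none from the protocol: normal scores, equal SD at both waves (set to 1), no mean change, a cutoff of 1.96, internal reliability α and pre-post correlation r.

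- Reliable-change threshold: 1.96 × √(2(1 − α)).
- SD of the natural difference: √(2(1 − r)).
- One-sided tail: Φ(−1.96 × √((1 − α)/(1 − r))).

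With α = 0.80 the threshold is 1.96 × √0.40 = 1.24 SD.

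| r | SD of difference | Reliably improved | Of 400 |
|---|---|---|---|
| 0.80 (equal to α) | 0.632 | 2.5% | 10 |
| 0.70 | 0.775 | 5.5% | 22 |
| 0.60 | 0.894 | 8.3% | 33 |
| 0.50 | 1.000 | 10.8% | 43 |

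The result depends on both inputs. At r = 0.60, α = 0.75 gives 6.1% (24 of 400) and α = 0.90 gives 16.4% (65 of 400). For a given r, higher internal reliability means more apparent improvers, because the threshold shrinks while natural movement does not. The rate passes 2.5% whenever r < α. By symmetry the same share would be classed as reliably deteriorated.

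**Clinical significance, two readings.**

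1. *Post score alone.* An adolescent who starts and stays in the normal range meets the illustrated criterion without changing.
2. *Reliable change plus crossing the cutoff.* That adolescent cannot qualify, but would still count in a denominator of all participants.

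A bivariate-normal simulation of the second reading (2 million draws, no app effect, α = 0.85) shows what the denominator does. The share starting above the cutoff is also assumed.

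| Share above cutoff at start | r | Qualify, of 400 | As % of all | As % of those above cutoff |
|---|---|---|---|---|
| 60.43% | 0.85 | 4.8 | 1.2% | 2.0% |
| 60.43% | 0.60 | 26.3 | 6.6% | 10.9% |
| 10% | 0.85 | 2.3 | 0.6% | 5.8% |
| 10% | 0.60 | 12.4 | 3.1% | 30.9% |

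Restricting the denominator is right in principle, but it exposes regression to the mean: an inert app could show up to 31% under these assumptions. The restricted rate needs a base rate with the same restriction.

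**The case against.** **A stronger reading is tempting.** A reader might infer that many participants are bound to count as successes without changing, and put a number on it. The Background says that "60.43% of Italian adolescents report an intense or a problematic social media (SM) use", so (1 − 0.6043) × 400 = 158 would start outside that range. The documents do not support this as a finding. The post-score criterion is introduced as an example and joined to reliable change by 'and', and the sentence is about classifying a change. If both conditions are required, no unchanged participant is counted. The 60.43% is a background prevalence that pools intense and problematic use. It is not a cutoff on the Bergen scale, the primary outcome, and the Background itself says that intense use may be normative. A narrower definition would raise the number, but the protocol fixes none.

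**The rates are assumed.** This is correct. Reliability, stability and the 1.96 cutoff are not in the protocol, and if stability equals reliability the excess disappears. What stands is the direction of the error when stability is lower, and the lack of anything planned that would show which case applies.

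**The earlier waves are already used.** The piecewise models take in T0 to T3, but they supply a reference for mean change only, not for the individual counts.

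**The pilot is modest in its claims.** It is called preliminary, and the limitations concede that a nonrandomized design restricts causal inference. That tempers the consequences, but the individual indices are still offered as added support for an app effect.

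**Details may sit in an analysis plan.** Exact cutoffs and the classification rule may well do so, and their absence is not held against the article. The interval and the internal-reliability basis are stated in the article itself.

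**Conclusion.** The point holds for the base rate. As written, the individual counts cover T2-T3 only, rest on internal reliability, and have no app-free comparison, so they cannot strengthen the evidence of an app effect. With no effect at all, the share reliably improved would be 2.5% if five-month stability equals internal reliability, and 5.5% to 10.8% at assumed α = 0.80 and r = 0.7 to 0.5.

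On clinical significance the point is conditional. The illustrated criterion needs no pathological start. Applied alone, it would count adolescents who were normal throughout; combined with reliable change and crossing, those adolescents cannot qualify and do not belong in the denominator. The text leans toward the combined rule but should say so.

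This is a worthwhile, inexpensive improvement to a supplementary analysis. It does not affect the feasibility thresholds or the mean-change models.

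**What to change.** - Compute the Reliable Change Index for T0-T1 and T1-T2 as well as T2-T3, in the same phase 3 participants, with the same reliability value and cutoff.
- Report improvement and deterioration for each interval, and the T2-T3 rates minus the app-free rates.
- Report clinically significant change only among those above the scale cutoff at T2, requiring both reliable change and crossing the cutoff. Apply the same restriction at the start of each app-free interval, so that regression to the mean enters the reference too.
- Describe the app-free intervals as a reference, not a control: season, repeated testing and loss of participants can still differ between intervals.

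**Cost.** The change is to analysis wording, with some extra computation. It needs no data beyond the planned waves; the Results section reports T0 and T1 complete as of July 2024, with later follow-up still planned. The downside is a smaller denominator for clinically significant change, hence a less precise rate, and the base rate is available only for participants with the earlier waves.
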